**Calculation rule for LA mixtures**
The app performs the following stepsCalculation of maximum safe volume for first LAThe user enters which volume of first LA is to be used (0–maximum volume)Calculation of corresponding maximum dose of first LA and determination of percentage of total maximum doseCalculation of maximum dose of second LA based on remaining percentage of total maximum doseCalculation of maximum volume of second LA

### Groups and Randomization

There will be 2 study groups: in the control group, participants will be asked to use the method they usually use in their clinical practice to calculate the maximum safe dose of LA; in the LoAD Calc (experiment) group, participants will be required to use the LoAD Calc app, which will be preinstalled on a standard Geneva University Hospitals (HUG) smartphone (Galaxy XCover 4s; Samsung) running on Android 11.

Stata’s (StataCorp LLC) replicable balanced randomization mechanism will be used to allocate participants to their study group. Textbox 2 contains the code that will be used.

Randomization code.
*set obs #N*

*egen arm = seq(), to(2)*

*set seed #S*

*gen random = uniform()*

*sort random*

Wherein “1” will be the control group, and “2” will be the LoAD Calc group.

Since randomization will be stratified according to participant position (either resident or registrar), 2 seeds (#S) will be used (07022023 and 20230207).

A sample size calculation will be used to determine the total number of observations. It will be rounded up to the nearest ten to enhance the study power and take into account attrition and potential exclusions. The stratified number of observations (#N) will be computed according to the proportion of potential participants belonging to both eligible positions (residents vs registrars).

The method used by the participants allocated to the control group to calculate the maximum safe dose of LA will be recorded. There will be no teaching or introductory intervention for any of the participants before the study, and the participants allocated to the LoAD Calc group will therefore discover the app while answering the first vignette.

### Web-Based Study Platform

A specific web-based platform will be developed using the Joomla! 4.3 content management system (Open Source Matters). It will be hosted on a Swiss server (Kreativmedia GmbH) and secured by the RSFirewall 3 (RSJoomla) and AdminTools 7 (Akeeba Ltd) components. To ensure participant anonymity, unique usernames and passwords will be created using Manytools’ web-based password generator [17]. These credentials will then be imported into Stata and allocated to either study group according to the randomization process described above. Finally, this data will be exported to a CSV file, which will be imported into the web-based study platform using the Import Joomla Users component (version 3.4; Lerus Ltd).

Consents, questionnaires, and vignettes will be managed using Shondalai’s Community Surveys 6 and Community Quiz 6 components (Bulasikku Technologies Pvt Ltd). All data will be stored on an encrypted MySQL-compatible database (MariaDB 10, MariaDB Foundation).

### Inclusion and Exclusion Criteria

All resident physicians and registrars working in the HUG anesthesiology department will be eligible for inclusion. The only exclusion criteria will be current or previous use of the LoAD Calc app. This criterion will be assessed by a screening question asked after the completion of all study vignettes.

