### Consent and Study Sequence

Participants will be asked to set their phones to flight mode. This will enable them to access any note, calculator, or app they use to calculate LA doses while avoiding potentially disruptive interruptions. The study itself will take place in a separate, quiet room. There, an investigator will prompt them to pick up a sealed, opaque envelope containing the credentials necessary to log in.

All participants will be asked to sign an electronic consent form immediately after logging in. Those who agree will proceed to a first questionnaire designed to gather demographical data (Textbox 3) and determine whether these participants are currently using LoAD Calc or if they have used this app before (exclusion criterion). After completing this questionnaire, an introductory screen giving information regarding the vignettes they are about to see and specifying the calculation method they are to use (LoAD Calc for the experimental group vs left at the participant’s will for the control group) will be displayed. At this stage, those allocated to the LoAD Calc group will be given the smartphone preinstalled with the LoAD Calc app.

First questionnaire.

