**Page 2: exclusion criterion**
Has heard of LoAD Calc (multiple-choice questions with only 1 acceptable answer)^a^Has installed LoAD Calc (multiple-choice questions with only 1 acceptable answer; branching logic will be used to avoid displaying irrelevant questions)Has used LoAD Calc (multiple-choice questions with only 1 acceptable answer; branching logic will be used to avoid displaying irrelevant questions; answering “yes” to either of those questions will lead to participant exclusion)Context of LoAD Calc use (multiple-choice question with only 1 acceptable answer; branching logic will be used to avoid displaying irrelevant questions)Has LoAD Calc still installed (multiple-choice question with only 1 acceptable answer; branching logic will be used to avoid displaying irrelevant questions)Still uses LoAD Calc (multiple-choice questions with only 1 acceptable answer; branching logic will be used to avoid displaying irrelevant questions; answering “yes” to either of those questions will lead to participant exclusion)

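### The only exclusion criterion is given two incompatible time points, one of them after the primary outcome is recorded, and both follow allocation

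*Protocol article*

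**What the plan says.** The Inclusion and Exclusion Criteria section states: "The only exclusion criteria will be current or previous use of the LoAD Calc app". It then fixes the timing: "This criterion will be assessed by a screening question asked after the completion of all study vignettes".

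The Consent and Study Sequence section gives a different order. After login and consent, a first questionnaire collects demographic data and serves to "determine whether these participants are currently using LoAD Calc or if they have used this app before (exclusion criterion". Only then does the method appear: "After completing this questionnaire, an introductory screen giving information regarding the vignettes they are about to see". The smartphone is handed over at that stage, and the vignettes follow. The textbox for this questionnaire has a page titled "Page 2: exclusion criterion", placed between consent and demographics, on which a positive answer about use "will lead to participant exclusion".

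The text after that textbox lists what follows the vignettes: the usability scale (LoAD Calc group), the methods used (control group) and a confidence rating (both groups). It contains no exclusion question.

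On allocation, the Web-Based Study Platform section says of the login credentials: "These credentials will then be imported into Stata and allocated to either study group according to the randomization process described above". On the study day, "an investigator will prompt them to pick up a sealed, opaque envelope containing the credentials necessary to log in".

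**The concern.** Two current statements give opposite timings for the single rule that decides who is eligible. Study staff cannot follow both, and the choice affects who is analysed.

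The after-vignettes timing is the more serious of the two. By then all responses that define the overdose rate have been given, and LoAD Calc participants have just worked through 10 vignettes with the app. A question about current or previous use no longer means the same thing in the two arms. Some LoAD Calc participants could answer yes because of the study itself, which is much less likely in the control arm. Eligibility would then depend partly on allocation.

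Even with the earlier timing, the question comes after the participant has taken a credential already assigned to an arm. Anyone excluded is a randomised participant removed from the comparison, and uses a place on an allocation list of fixed length per stratum. Since recruitment is face to face on the same day, this is avoidable.

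**Working it through.** **Order of events under each version**

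1. Credentials are allocated to arms in Stata and imported into the platform (Web-Based Study Platform).
2. The participant picks up an envelope, logs in and consents (Consent and Study Sequence).
3. First questionnaire, with the exclusion page. *Questionnaire version: eligibility is settled here.*
4. The introductory screen names the method; the LoAD Calc group receives the phone.
5. The 10 vignettes are answered; the primary outcome data exist.
6. Post-vignette items. *Inclusion and Exclusion Criteria version: eligibility is settled here.*

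Both points come after step 1, so exclusions are post-randomisation either way. What differs is what has happened in between. At step 3 the participant has not been shown the method and has no outcome data, and the question is identical in both arms. At step 6 the arms differ in exposure to the very thing asked about, and the outcome is recorded.

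**Does the loss of participants threaten power?**

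Inputs from Results and Statistical Analysis: difference 10%, SD 10%, two-sided alpha 0.05, power 90%, 23 per group, target 50. Power is taken from the noncentral t distribution with n1 + n2 − 2 degrees of freedom and noncentrality (10/10)/√(1/n1 + 1/n2).

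- The plan's figure reproduces: 23/23 gives noncentrality 3.391 and power 0.912; 22/22 gives 0.8997, just short. So 46 is right under its own assumptions.
- The allowance is 50 − 46 = 4, or 4/50 = 8%.
- If the strata are set in proportion to 62 residents and 52 registrars, 50 × 62/114 = 27.2 and 50 × 52/114 = 22.8, so 27 and 23. The printed code alternates arms 1 and 2, giving 14/13 and 12/11: 26 control and 24 LoAD Calc. The article does not print these stratum sizes, so this split is an assumption.

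| Control / LoAD Calc | Situation | Power |
|---|---|---|
| 25/25 | equal split, no exclusions | 0.934 |
| 26/24 | assumed split, no exclusions | 0.933 |
| 26/22 | two LoAD Calc exclusions | 0.922 |
| 26/20 | four LoAD Calc exclusions | 0.908 |
| 20/20 | 20% excluded, evenly | 0.869 |
| 25/15 | 20% excluded, all from one arm | 0.847 |

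At 10% excluded (45 left, evenly split), power is 0.906. The exclusion rates are assumed; the article gives none.

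**The case against.** The strongest reply is that the detailed sequence is clear. The questionnaire textbox is set out page by page, and nothing after the vignettes asks about exclusion, so the sentence in Inclusion and Exclusion Criteria looks like an isolated slip. Under the detailed sequence the trait pre-dates the study, envelopes are sealed and opaque, and the question precedes disclosure of the method. This stands: that version costs allocated places and creates little selection bias. It does not remove the contradiction, because the slip sits in the section a reader consults for eligibility.

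Four stronger readings are tempting and are not supported:

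- *The whole LoAD Calc arm would be excluded.* Taken literally, the post-vignette question would be true for all of them. But Groups and Randomization says they discover the app at the first vignette, and the questionnaire asks about installation, context of use and continued use. Use before the study is evidently meant. The risk is some differential answering, not loss of an arm.
- *Asking about the app defeats the concealment of the two arms.* Study Design says only that participants are not told there are two arms. A question about an app is at most a hint.
- *The trial becomes underpowered.* The table shows power above 90% with four LoAD Calc exclusions. It falls below 0.87 only if an assumed 20% are lost. The Results section also names a pool of 114 and a fallback to other hospitals.
- *The 26/24 split is a defect.* It rests on unprinted stratum sizes and costs almost nothing (0.933 against 0.934).

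Nor is a high number of prior users established. The app was developed at this hospital, but the abstract describes testing before clinical deployment, and no usage figure is given.

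**Conclusion.** The point holds as a contradiction about when eligibility is determined. If the Inclusion and Exclusion Criteria sentence is followed, eligibility is decided after the primary outcome is recorded and after exposure in one arm only, so exclusions can differ by arm and bias the comparison. If the questionnaire sequence is followed, exclusions remain post-randomisation, but the damage is mainly used-up allocations. A reader might infer that the randomised comparison is broken under either version; that fits only the after-vignettes one.

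Neither the direction nor the size of any bias can be computed, because the documents give no prior-use rate and do not show how participants would interpret the question. The case for correcting this rests on validity and on having one executable rule, not on sample size.

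**What to change.** Delete the sentence that places screening after the vignettes and state one time point throughout.

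Preferably, ask at recruitment, before the envelope is picked up, and word the question as use before the study day. Placing the app within a list of local anesthetic dose calculators avoids singling it out. Ineligible people then never take an allocated credential.

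If screening stays in the first questionnaire, keep it before the method is disclosed, use the same before-the-study-day wording, report exclusions by arm, and analyse all consenting, eligible participants as randomised. Defining the analysis set as everyone who opened an envelope would not work: consent is signed after login, so that set would include people who had not consented.

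The cost is small: revised wording, a brief question before electronic consent if screening moves to recruitment, and a change to a platform already built and tested. The Results section leaves room for adjustments before recruitment starts.

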### Recruitment

The project will first be presented to the head of the anesthesiology department and then to all consultants. After obtaining their agreement, investigators will recruit potential participants directly in the operating room. These residents and fellows in anesthesiology will be informed that the study will last at most 1 hour and that an investigator will replace them in the operating room while they participate. They will be told that participation is entirely voluntary, that there will be no consequence if they refuse to participate, and that they will be able to withdraw at any time without explanation. No incentive other than advancing scientific knowledge will be given to promote participation. They will be given a paper sheet summarizing the information regarding the study and data protection (Multimedia Appendix 2). Those who agree will be scheduled for participation on the same day. Together with the anesthesiology consultant overseeing the operating room, an investigator will organize replacements to avoid any disruption in the operating program. There will be only 1 slot, and therefore, only 1 participant per hour.

### Consent and Study Sequence

Participants will be asked to set their phones to flight mode. This will enable them to access any note, calculator, or app they use to calculate LA doses while avoiding potentially disruptive interruptions. The study itself will take place in a separate, quiet room. There, an investigator will prompt them to pick up a sealed, opaque envelope containing the credentials necessary to log in.

All participants will be asked to sign an electronic consent form immediately after logging in. Those who agree will proceed to a first questionnaire designed to gather demographical data (Textbox 3) and determine whether these participants are currently using LoAD Calc or if they have used this app before (exclusion criterion). After completing this questionnaire, an introductory screen giving information regarding the vignettes they are about to see and specifying the calculation method they are to use (LoAD Calc for the experimental group vs left at the participant’s will for the control group) will be displayed. At this stage, those allocated to the LoAD Calc group will be given the smartphone preinstalled with the LoAD Calc app.

First questionnaire.
**Page 1: consent**
Consent to participate and to data reuse (multiple-choice questions with only 1 acceptable answer)
**Page 2: exclusion criterion**
Has heard of LoAD Calc (multiple-choice questions with only 1 acceptable answer)^a^Has installed LoAD Calc (multiple-choice questions with only 1 acceptable answer; branching logic will be used to avoid displaying irrelevant questions)Has used LoAD Calc (multiple-choice questions with only 1 acceptable answer; branching logic will be used to avoid displaying irrelevant questions; answering “yes” to either of those questions will lead to participant exclusion)Context of LoAD Calc use (multiple-choice question with only 1 acceptable answer; branching logic will be used to avoid displaying irrelevant questions)Has LoAD Calc still installed (multiple-choice question with only 1 acceptable answer; branching logic will be used to avoid displaying irrelevant questions)Still uses LoAD Calc (multiple-choice questions with only 1 acceptable answer; branching logic will be used to avoid displaying irrelevant questions; answering “yes” to either of those questions will lead to participant exclusion)

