### Study Design

This will be a monocentric, parallel-group, randomized controlled trial based on clinical vignettes. The protocol was developed according to the Standard Protocol Items: Recommendations for Interventional Trials (SPIRIT) statement (Multimedia Appendix 1) [14]. Given its design, the investigators will not be blinded as to the intervention. Nevertheless, participants will not be informed that there are 2 different arms and will not be told the exact outcomes studied, even though they will be provided with general information regarding the study. In addition, the data analyst will be blinded as to participant allocation by renaming the groups before sending data for statistical analysis. Randomization will be stratified according to current position (resident vs registrar).

Results will be reported according to the CONSORT-EHEALTH (Consolidated Standards of Reporting Trials of Electronic and Mobile HEalth Applications and onLine TeleHealth) guidelines [15]. Relevant elements of the CHERRIES (Checklist for Reporting Results of Internet E-Surveys) will be included since web-based questionnaires will be used in the course of this study [16].

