## Results

The 10 vignettes necessary to carry out the study were successfully created, and the maximum safe doses were determined. These vignettes and the doses were checked and approved by all authors. The 10 vignettes, as well as their English translation, were presented to peer reviewers but are not publicly available to avoid any potential bias. They will nevertheless be published along with the results paper.

The sample size calculation was performed using Stata (version 17.0). It showed that 46 participants (23 in each group) would be needed to detect a 10% difference with a power of 90%, taking into account an SD of 10%. In line with the above methods, a total of 50 anesthesiologists should therefore be recruited. Since there are 62 residents and 52 registrars in the HUG Anesthesiology Department, a participation rate of 44% (50/114) will be necessary. This participation rate seems achievable with the aforementioned recruitment procedure. If this rate cannot be achieved, other Swiss University hospitals will be contacted, and similar recruitment procedures will be carried out to obtain the required sample size.

The study platform has been successfully created and tested by all coauthors [22]. The data extraction mechanisms have also been successfully checked.

The recruitment will take place once this study protocol has been reviewed and accepted for publication to allow for any necessary adjustments before study inception. The current version of the protocol is 0.9 (October 10, 2023). The published version will be 1.0.

It should be possible to start recruitment during the winter of 2023. This would allow data analysis to take place in spring 2024, and results should be submitted for publication in an international peer-reviewed journal by the end of the same year.

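### The protocol gives two incompatible times for the LoAD Calc screening questions, and the pre-vignette version names the tested app to every control before the task

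*Protocol article*

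**What the plan says.** Three places describe when prior use of LoAD Calc, the only exclusion criterion, is established.

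- **Inclusion and Exclusion Criteria** puts it at the end: "This criterion will be assessed by a screening question asked after the completion of all study vignettes".
- **Consent and Study Sequence** puts it at the start. The first questionnaire, completed after electronic consent, is meant to collect demographic data and to "determine whether these participants are currently using LoAD Calc or if they have used this app before (exclusion criterion". The vignettes come later: "After completing this questionnaire, an introductory screen giving information regarding the vignettes they are about to see". That introductory screen also tells each group which calculation method to use, and controls are left free to choose.
- **The first-questionnaire textbox** gives the layout: consent on page 1, LoAD Calc on page 2, demographics on page 3. Page 2 lists six items, all about LoAD Calc. The first is "Has heard of LoAD Calc (multiple-choice questions with only 1 acceptable answer". Each of the other five carries the note that "branching logic will be used to avoid displaying irrelevant questions".

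On masking, Study Design states that investigators are not blinded but that "participants will not be informed that there are 2 different arms and will not be told the exact outcomes studied". It adds that participants do receive general information about the study.

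**The concern.** The same criterion cannot be assessed by a question after all vignettes and also by a page that precedes them. The choice matters because only one of the two orders keeps the app's name away from controls until their answers are in.

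Under the earlier timing, a control is asked about one named product and no other, fills in demographics, and is then told to use whatever method they prefer. It is a short step to conclude that the product is what the study is about and that other participants are given it. Withholding the existence of two arms is the protocol's participant-side safeguard in a trial with unblinded investigators, and it loses much of its value if the questionnaire invites participants to work it out.

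Controls who see themselves as the comparator may try harder, take more or less time, or rate their confidence differently. Time taken and confidence are secondary outcomes. The primary outcome, the overdose rate, also depends on how carefully each participant calculates.

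**Working it through.** **1. Timing, side by side.**

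| Place in the protocol article | When LoAD Calc use is asked | Form |
|---|---|---|
| Inclusion and Exclusion Criteria | after all vignettes | one screening question |
| Consent and Study Sequence | after consent, before the introductory screen and vignettes | part of the first questionnaire |
| First-questionnaire textbox | page 2 of 3, before the vignettes | six listed items |

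One place says after and two say before. The Results section reports that the platform has been built and tested, so one order is presumably already implemented. The article does not say which.

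**2. What a control would see under the earlier timing.** Six items are listed. Item 1 has no branching note, and items 2 to 6 do. Exposure is therefore at least one item and at most six. Someone who has never heard of the app would presumably see only item 1. The items on context of use and on current use concern users, who are excluded, so controls who stay in the analysis would not see the whole set. One item is enough to show the name. With 1:1 allocation of 50 participants, 50 / 2 = 25 controls would see it.

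**3. What the masking statement covers.** It covers two things: the existence of two arms and the exact outcomes. Page 2 states neither. Any loss of concealment is by inference, from a page about a single product followed by a free choice of method.

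**4. Does any stated figure change?** The Results section gives 46 participants (23 per group) for a 10% difference, SD 10%, power 90%. The Statistical Analysis section sets a two-sided 5% level.

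- Normal approximation: n per group = 2 × (1.960 + 1.282)² × (10/10)² = 21.0, rounded up to 22, or 44 in total.
- Two-sample t-test: 22.02, rounded up to 23, or 46 in total, with power 0.912 at 23 per group.

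The stated 46 is reproduced. The order of the questionnaire does not enter this calculation, so moving the items leaves it unchanged.

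**5. Illustration only.** The documents give no basis for how far cueing might move the results. *If* controls tried harder and the true difference shrank from 10 points (an assumption), t-test power with SD 10 would be:

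| True difference | 23 per group | 25 per group |
|---|---|---|
| 9 | 0.85 | 0.88 |
| 8 | 0.76 | 0.79 |
| 7 | 0.64 | 0.68 |

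The opposite reaction, less effort from controls who feel passed over, would widen the difference instead. The table shows what would be at stake under one direction and is not an estimate.

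**The case against.** The strongest reply is that the protocol already contains the timing that removes the problem. If the exclusion section governs, no control reads the app's name before the task. That is right, and it is why the contradiction is the firm part of this point and disclosure is its consequence. It does not dispose of the matter, because the detailed sequence and the questionnaire layout both say the opposite.

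Other replies also have weight. The primary outcome is scored against doses fixed in advance, so cueing cannot affect the scoring, only the participant's own work. The information sheet is not shown and may already name the app. The app was developed at the same hospital, so some staff will know it anyway. These limit the likely effect but give no reason to prefer the earlier timing.

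Two stronger readings are tempting and are not supported.

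- *That page 2 breaches the stated masking.* A reader might infer this, but Study Design does not promise to hide the app's name, and the page reveals neither the arms nor the outcomes.
- *That word of the app would spread, lead colleagues to try it, and exhaust the margin of 50 − 46 = 4 participants through exclusions.* The documents give no rate for this. Falling to 45 (23 + 22) would leave t-test power at 0.906. The Results section provides for recruiting at other Swiss university hospitals if needed. Participants in the LoAD Calc group use the app throughout and can name it to colleagues however the screening is worded.

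**Conclusion.** The point holds as a documented contradiction with a plausible consequence for masking. The timing of the LoAD Calc screening must be reconciled across three places. If the pre-vignette order is the one used, all controls, about 25, see the tested app named before they start, and the concealment of the two arms is weakened by inference.

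The size and direction of any effect on overdose rate, time or confidence cannot be derived from the documents, and no stated figure is wrong because of it. The conclusion assumes that item 1 is shown to everyone, as the absence of a branching note implies, and that the unseen information sheet does not already disclose the app.

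**What to change.** Adopt the timing in Inclusion and Exclusion Criteria and make the rest agree with it.

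- Move every item that names LoAD Calc to after the last vignette. Correct Consent and Study Sequence, the first-questionnaire textbox and the built platform accordingly. Leave consent and demographics where they are.
- Give both arms the same items, worded as hearing of, installing or using the app *before today's session*. Without that wording, everyone in the LoAD Calc group would report use and meet the exclusion criterion.
- Ask participants not to discuss the session with colleagues until recruitment closes. Rewording the screening cannot stop the LoAD Calc group from naming the app, so this request is needed as well.

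Keeping the question early but hiding LoAD Calc in a list of dosing tools is not an equivalent solution. The list would still name the app, and it would show controls other tools shortly before the task, when the phone set-up is such that "This will enable them to access any note, calculator, or app they use to calculate LA doses".

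The cost is small: moving one questionnaire page, rewording its items and adding one instruction. The downside is that prior users are identified only after completing the vignettes, so their session time is spent on data that will be excluded.
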